**Methods:**

This is a prospective, single-center observational trial. 276 FGIDs outpatients who visit Peking Union Medical College Hospital will be evaluated simultaneously by HADS and vibraimage technology, then to evaluate the screen efficacy of this technology. The patients will be allocated into two groups (those with or without psychological disorders). The primary endpoint is the overall rate of improvement, specifically referring to the proportion of patients who achieved Likert scores greater than or equal to 4. The secondary endpoints encompass evaluating whether there is a reduction of more than 50% in symptom evaluation scores such as IBS-SSS. Additionally, the study will assess changes in health status and quality of life using SF-36 questionnaires and the patients’ satisfaction with treatment. Furthermore, psychological status will be reassessed by vibraimage technology and HADS after treatment to evaluate the effect of combined psychological factors on FGIDs treatment.

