#### The assessment of patient prognosis and satisfaction

2.6.2

The patients will be divided into two groups according to HADS, that is with or without psychological disorder group. The patients in both groups will receive the conventional treatment, without any additional interventions beyond the standard care for FGIDs. The treatment effect questionnaire will be administered after 4 weeks. Overall improvement will be evaluated using a 5-point Likert scale (36), where patients will be prompted to complete the following statement: “How does my gastrointestinal condition compare to before I commenced treatment at the clinic?” The response options include: deteriorated, slightly deteriorated, unchanged, slightly improved, and significantly improved. The HADS and vibraimage technology will also be systematically evaluated.

Primary endpoint: the overall rate of improvement, specifically referring to the proportion of patients who achieved Likert scores greater than or equal to 4.

Secondary endpoint: HADS and vibraimage technology outcomes, along with the improvement degree of FGIDs symptom scores such as IBS-SSS, quality of life by SF-36 questionnaires, and the patients’ satisfaction with treatment.

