### Descriptive statistics

2.9

The consistency analysis is conducted based on Gwet’s Agreement Coefficient 1 (AC1, 38) to assess the concordance between vibraimage technology and HADS detection results, as well as to determine the optimal threshold for vibraimage technology. Specifically, a HADS-A score of 8 or higher indicates anxiety, while a HADS-D score of 8 or higher suggests depression (10).

The measurement data that conform to a normal distribution are represented by *x̄* ± *s*, while the ones that do not conform are represented by the median (interquartile range). The difference between the two groups of measurement data following a normal distribution is assessed using a student *t*-test, whereas the difference between the two groups of measurement data not following a normal distribution is assessed using Mann–Whitney U test. The difference between the two groups is evaluated using *χ*^2^ test. Oneway-ANOVA analysis is employed for group comparisons. Pearson correlation analysis is used for measurement data with a normal distribution, and Spearman correlation analysis is used for measurement data without a normal distribution.

In the process of conducting binary logistic regression analysis to determine whether patients with FGIDs are also affected by psychological disorders, we will continuously enhance the model’s goodness of fit by eliminating irrelevant independent variables. Subsequently, a diagnostic model with high diagnostic efficiency will be derived. Finally, a Receiver Operating Characteristic (ROC) curve will be constructed based on the performance of sensitivity and specificity at various thresholds. This analysis will aid in identifying the optimal diagnostic test threshold and in evaluating the accuracy, sensitivity, and specificity of the test.

Variables with a *p* value <0.05 are considered statistically significant. The statistical analysis will be conducted by a medically trained personnel who will remain blinded to the assignment of study groups. The data statistics in our study will be conducted using paper questionnaires. In the event of missing items, we will either discard the questionnaire or, if necessary, employ imputation techniques to fill in the missing values.

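### Baseline HADS defines the two groups and follow-up HADS is also an endpoint, so a between-group test of HADS, as level or as change, cannot inform on treatment response

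*Protocol article*

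**What the plan says.** Section 2.6.2 of the protocol article forms the groups: "The patients will be divided into two groups according to HADS, that is with or without psychological disorder group". Section 2.1 says the same. Section 2.9 gives the cut-offs: "a HADS-A score of 8 or higher indicates anxiety, while a HADS-D score of 8 or higher suggests depression". It does not say how the two subscales combine into one grouping.

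HADS is measured again after treatment, and section 2.6.2 makes it an endpoint of the comparison: "Secondary endpoint: HADS and vibraimage technology outcomes, along with the improvement degree of FGIDs symptom scores such as IBS-SSS". The abstract states the purpose: "psychological status will be reassessed by vibraimage technology and HADS after treatment to evaluate the effect of combined psychological factors on FGIDs treatment". Neither place says whether the week-4 score or the change from baseline is analysed.

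For measurement data in two groups, section 2.9 begins "The difference between the two groups of measurement data following a normal distribution is assessed using a student" t-test and gives Mann–Whitney for non-normal data. It also lists one-way ANOVA, which with two groups is the t-test again, and Pearson and Spearman correlation. The only regression model named predicts psychological disorder, not a follow-up outcome.

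On symptom scores, the abstract speaks of "whether there is a reduction of more than 50% in symptom evaluation scores such as IBS-SSS", which is a yes/no outcome. Section 2.6.2 speaks of the degree of improvement.

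**The concern.** When a variable defines the groups, its later values cannot also serve as an ordinary outcome of comparing them.

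- **Week-4 level.** Patients selected for high HADS will on average still be higher four weeks later. The test detects the selection.
- **Change.** Some patients cross the cut-off on a transient high or low score. On re-measurement the high group drifts down and the low group drifts up with no real change in anyone.

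The abstract intends the reassessment to show how psychological factors bear on treatment. An artefactual fall in the comorbid group could be read as psychological benefit from gastrointestinal treatment alone, or as a real difference in response between the groups. Neither reading would be evidence, whichever way it is used in the argument for multidisciplinary care.

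**Working it through.** **Sample size used.** Section 2.7 gives 98 patients for the follow-up comparison. From 57% and 57%/2 = 28.5%, two-sided α 0.05, power 0.80, unpooled variance:

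n per group = (1.96 + 0.8416)² × (0.57×0.43 + 0.285×0.715) / 0.285² = 7.849 × 0.4489 / 0.0812 = 43.4, so 44. Then 44/0.9 = 48.9, so 49 per group and 98 in total.

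The stated figure reproduces. How many of the 276 are followed up is in a figure not shown, so 88 (98 less dropout) and 251 are also used below.

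**Assumptions not in the document.** HADS is normal with equal mean and SD at both visits, there is no true change, and test-retest correlation r is 0.7, 0.8 or 0.9. Points are given for SD = 4. The 50:50 split follows the 50% prevalence in section 2.7.

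**Case 1: one score split at its median.** Group means lie ±0.798 SD from the overall mean.

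*Level.* Baseline gap = 2 × 0.798 = 1.596 SD. Week-4 gap = r × 1.596 = 1.12 / 1.28 / 1.44 SD, or 4.5 / 5.1 / 5.7 points. In simulation the test rejects in 100% of runs. This is the baseline gap carried forward; regression to the mean makes it smaller.

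*Change.* Gap in mean change = 2 × (1 − r) × 0.798 SD. Within-group variance of change = (1 − r)² × (1 − 0.798²) + (1 − r²). Standard error = SD × √(2/49).

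| r | Gap (SD) | Gap (points) | SD of change | SE | z | P(reject) = Φ(z − 1.96) |
|---|---|---|---|---|---|---|
| 0.7 | 0.479 | 1.9 | 0.737 | 0.149 | 3.22 | 90% |
| 0.8 | 0.319 | 1.3 | 0.612 | 0.124 | 2.58 | 73% |
| 0.9 | 0.160 | 0.6 | 0.440 | 0.089 | 1.79 | 43% |

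Simulation with the actual t-test gives about 88% / 71% / 43% at 98 patients, 86% / 68% / 38% at 88, and 99.9% / 99% / 81% at 251.

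**Case 2: either subscale at 8 or more qualifies.** This further assumes 50% positive overall, a between-subscale correlation of 0.55, and independent measurement errors in the two subscales. Selection on each subscale is then weaker. The gap in change per subscale is about 0.26 / 0.17 / 0.09 SD, and the test rejects in about 39% / 26% / 17% of studies at 98 patients. Shared errors between subscales would raise these rates towards those of case 1.

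**Other scores** (own reliability 0.7, HADS reliability 0.8, no true change).

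- Change test, errors independent of the HADS error: about 5%, which is nominal.
- Change test, error correlation 0.3: 12% at 98 patients and 23% at 251. At 0.5: 22–24% and 49–51%.
- Raw week-4 test, true level correlated 0.4 with HADS: 66% and 97%, through a standing baseline difference.
- Week-4 score regressed on group and its own baseline, independent errors: at true-level correlation 0.4, 17% at 98 and 37% at 251; at 0.6, about 34% and 72%.

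**Symptom endpoint.** No arithmetic is needed. A reduction of more than 50% and a degree of improvement call for different analyses and can give different answers. Section 2.3 assigns different instruments by FGID subtype.

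**The case against.** The strongest reply is that the article never says HADS will be tested between the groups. Section 2.9 is a general list of tests, not tied to the endpoints in 2.6.2, and an analysis plan not shown may handle this properly. That limits the point to a conditional one, but does not remove it. The document itself makes HADS both the grouping variable and an endpoint of the comparison, and the two-group tests it names are unadjusted. An analysis plan that follows it inherits the problem on either reading.

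A second reply is that case 1 is the severe one. This stands: under an either-subscale rule the rates are roughly half or less, though still three to eight times nominal (17/5 = 3.4; 39/5 = 7.8).

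A reader might also infer that regression to the mean will produce false differences in every week-4 score. The document does not support that. Change in vibraimage, SF-36 or symptom scores stays near 5% unless their errors correlate with the HADS error, and a raw week-4 difference is a persisting baseline difference. Nor does the point reach the primary endpoint: the Likert item asks patients to compare now with before and has no baseline value. Pooling of symptom scores across instruments might be inferred too, but it is nowhere stated. The two symptom definitions could be read as one measure of the other, so that part is a call for clarity, not proof of a conflict.

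**Conclusion.** The point holds for HADS only. A between-group test of week-4 HADS is uninformative by construction. A test of HADS change has, with no true change, a false-positive rate at 98 patients of about 88% / 71% / 43% (one score split at its median) or 39% / 26% / 17% per subscale (either subscale qualifies), for correlations of 0.7 / 0.8 / 0.9. The correlations, normality and subscale structure are assumptions. The direction of the bias does not depend on their exact values; its size does. The endpoint is secondary, and the sample size of 98 is unaffected. Separately, the symptom-score endpoint is worded in two ways and should have one definition.

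**What to change.** 1. In 2.6.2 and 2.9, state that neither HADS level nor HADS change will be tested between the HADS-defined groups.
2. Report HADS by group at both visits descriptively, with a caveat on regression to the mean, and draw no conclusion on treatment effect from it.
3. Relate HADS change to vibraimage change across all patients. Correlation is already listed in 2.9.
4. Use one definition of the symptom-score endpoint in the abstract and 2.6.2, applied within each instrument.

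A baseline-adjusted group comparison should not be required for the other scores. In these non-randomised groups it can itself produce differences with no true change, as the last check on other scores shows. Adjusting HADS for its own baseline restores an error rate of 4% to 6% in the single-score case, but group is then almost a function of that baseline and the term tests only a jump at the cut-off.

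The cost is one between-group secondary test and some wording. All baseline values are already to be collected.

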### Baseline data collection

2.3

Vibraimage data specialist is responsible for collecting and analyzing the patient’s vibraimage technology data, while the HADS assessment specialist will handle the general information collection and analysis of the patient’s HADS self-rating data. Both specialists are unaware of each other’s datasets. The physicians will solely administer conventional treatments based on FGIDs diagnostic criteria, without any knowledge of the results obtained from vibraimage technology or HADS questionnaires.

The following information will be collected: demographic data (age, gender, height, weight), marital and childbearing status, occupation and education level; disease-related details including course of illness, diagnosis and classification of FGIDs, treatment process, and dietary habits. The FGIDs symptoms will be generally assessed by5-point Likert score. Patients diagnosed with irritable bowel syndrome will be evaluated based on their IBS Severity Score (IBS-SSS) (19); patients with functional dyspepsia, as well as those with constipation, will be assessed using the relevant symptom scores (20, 21); while patients with other functional disorders will be evaluated through the Gastrointestinal Symptom Severity Index (GISSI) (22). Baseline questionnaires will be administered to assess anxiety and depression levels using the Hospital Anxiety and Depression Scale (HADS), and general health-related quality of life using the Health Status Questionnaire (SF-36) (23).

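### The symptom-score secondary endpoint rests on a different instrument for each FGID subtype, is worded two ways, and is given only tests that ignore subtype

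*Protocol article*

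**What the plan says.** Section 2.3 of the protocol article first gives a measure for everyone: "The FGIDs symptoms will be generally assessed by5-point Likert score". It then assigns graded severity scores by diagnosis:

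- IBS: "Patients diagnosed with irritable bowel syndrome will be evaluated based on their IBS Severity Score (IBS-SSS".
- Dyspepsia and constipation: "patients with functional dyspepsia, as well as those with constipation, will be assessed using the relevant symptom scores".
- The remainder: "while patients with other functional disorders will be evaluated through the Gastrointestinal Symptom Severity Index (GISSI".

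Section 2.6.2 compares patients with and without psychological disorder, as classified by HADS. Its primary endpoint is "the proportion of patients who achieved Likert scores greater than or equal to 4", from one question put to all patients at 4 weeks. Among the secondary endpoints it lists HADS and vibraimage results "along with the improvement degree of FGIDs symptom scores such as IBS-SSS, quality of life by SF-36 questionnaires".

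The Methods paragraph of the abstract words the symptom endpoint differently: "The secondary endpoints encompass evaluating whether there is a reduction of more than 50% in symptom evaluation scores such as IBS-SSS".

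Section 2.9 gives the group comparisons. For continuous data it says "The difference between the two groups of measurement data following a normal distribution is assessed using a student" t-test, with Mann-Whitney U as the non-normal alternative and chi-square for proportions. None is stratified or adjusted by subtype. The only regression described models the presence of psychological disorder, not response to treatment.

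**The concern.** Two features combine. First, what a patient must do to count as improved depends on the instrument, and the instrument depends on the diagnosis. Second, the two groups are formed by HADS and not by randomisation, so nothing makes the share of IBS, dyspepsia, constipation and other disorders equal in them.

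A fall of more than 50% is free of units, so it can be stated for any instrument. It need not be equally easy to reach on each, because instruments differ in content and floor, and subtypes may differ in response to conventional care. If one HADS group holds more patients on an instrument where the threshold is easier, its crude responder rate rises with no psychological effect at all. The result could then be read as an influence of psychological comorbidity on symptom response, which is what this part of the study sets out to examine.

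The two wordings add to this. A responder proportion and a degree of improvement are different quantities with different tests, and section 2.6.2 does not carry the 50% rule.

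**Working it through.** **The plan's own figure.** Section 2.7 gives 98 patients for the follow-up comparison, from improvement rates of 57% and half of that (28.5%), two-sided α 0.05 (sidedness assumed), power 0.80 and 10% loss. With unpooled variance:

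n per group = (1.96 + 0.842)² × (0.57×0.43 + 0.285×0.715) / 0.285² = 7.849 × 0.4489 / 0.0812 = 43.4, so 44.

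44 / 0.9 = 48.9, so 49 per group and 98 in total. The figure reproduces. It is built on the overall improvement rate, which is the Likert endpoint, so this point does not touch it.

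**Group sizes.** 98 less 10% is 88, or 44 per group. If the whole cohort is followed, 276 less 10% is 248, or 124 per group at the 50% prevalence in section 2.7. Both are run.

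**Assumptions (none is in the article).** Four instruments with responder rates 50/40/30/20% under the 50% rule, the same in both HADS groups, so there is no true difference within any subtype. One group has a 25/25/25/25% mix. The other has 35/30/20/15% or 45/30/15/10%.

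**Crude bias** = Σ (mix × rate) in one group minus the same in the other.

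- Even mix: 0.25 × (0.50+0.40+0.30+0.20) = 0.350.
- 35/30/20/15%: 0.175+0.120+0.060+0.030 = 0.385, a bias of 3.5 points.
- 45/30/15/10%: 0.225+0.120+0.045+0.020 = 0.410, a bias of 6.0 points.

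**False-positive rate of the unstratified chi-square.** With d the bias, SE₀ the pooled and SE₁ the unpooled standard error:

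P(reject) ≈ Φ((d − 1.96·SE₀)/SE₁) + Φ((−d − 1.96·SE₀)/SE₁)

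Example: d = 0.060, n = 124. SE₀ = √(2×0.38×0.62/124) = 0.0616 and SE₁ = √((0.35×0.65 + 0.41×0.59)/124) = 0.0615. The first term is Φ(−0.988) ≈ 0.162 and the second about 0.002, together 0.163.

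| Mix in second group | Bias | 44 per group | 124 per group |
|---|---|---|---|
| 25/25/25/25% | 0 | 5.0% | 5.0% |
| 35/30/20/15% | 3.5 points | 6.3% | 8.8% |
| 45/30/15/10% | 6.0 points | 8.9% | 16.3% |

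Simulating the test itself gives about 7 to 9% at 44 per group and 9 to 17% at 124, in line with the approximation. A Cochran-Mantel-Haenszel test stratified by subtype stays near 5% in the same settings.

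**Sensitivity to the rates.** If responder rates span 10 points instead of 30, the bias is 1.2 to 2.0 points and the false-positive rate 5.1 to 6.2% over both group sizes. If rates are equal across instruments, the bias is zero and the rate 5% whatever the mix.

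**The case against.** The strongest reply is that the article does give every patient a common measure and makes a common Likert item primary. A reader might infer from the instrument list that no symptom measure covers the whole cohort. Section 2.3 (the general Likert score) and section 2.6.2 (the primary endpoint) contradict that. Only a graded severity score common to all subtypes is lacking.

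The second reply is that the abstract's 50% rule removes the units. This is right. A reader might conclude that unlike scales spoil the comparison however improvement is defined, even when every subtype responds alike. That does not follow: with equal responder rates across instruments there is no bias. What remains is confounding by subtype and instrument, and it needs both unequal mix and unequal attainability.

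The third reply is that section 2.9 is a general list of tests and the article never says raw score changes will be pooled; the plural scores in section 2.6.2 could be analysed within subtype. This stands too. Pooling raw changes would be worse. With assumed scale ranges of 500/24/24/100 and an equal 20% improvement on each, false positives would be 8 to 19% at 44 per group and 15 to 43% at 124. But these figures describe an analysis that the article does not state, and they are not charged against it.

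What the replies leave is text that is present, not detail left to a fuller document: two wordings of one endpoint, and named two-group tests that take no account of subtype.

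**Conclusion.** The point holds as a conditional risk to one secondary endpoint. The article words that endpoint in two ways, rests it on diagnosis-specific instruments, and names only tests that ignore subtype in non-randomised groups. On the 50% rule, the assumed scenarios give a bias of 0 to 6 percentage points and a false-positive rate from 5% up to about 9% (44 per group) or about 17% (124 per group). The upper ends need both a 30-point span in responder rates and the more unequal mix. Bias is not demonstrated, because the article gives neither quantity. The Likert primary endpoint and the sample size of 98 stand outside this point. Severity is low.

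**What to change.** In section 2.6.2, define the symptom endpoint as in the abstract: a reduction of more than 50% from baseline on the patient's own instrument.

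In section 2.9, state that the HADS groups are compared on this endpoint with a Cochran-Mantel-Haenszel test stratified by FGID subtype (which fixes the instrument), or with logistic regression including a subtype term. Show responder rates per instrument beside the combined result.

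If a graded change is also analysed, do it within instrument, or combine by a van Elteren test stratified by instrument or a model of standardised change with instrument as a factor. State that raw changes are not pooled across instruments.

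The cost is wording and slightly more analysis, since section 2.3 already records diagnosis and classification. The drawback is small strata: at 44 per group, a subtype with a 10% share has about 4 patients in that group (0.10 × 44 = 4.4), so its separate result will be descriptive only.

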### Sample size calculation

2.7

The sample size required for a trial comparing the efficacy of HADS and vibraimage technology in detecting comorbid psychological disorders in FGIDs patients is calculated here. Based on a literature search, it is evident that the prevalence of psychological disorders in FGIDs is 50%. Referring to previous methodological studies (22), we assume a sensitivity of 80% for vibraimage technology, a significance level (*α*) of 0.05, a test power (1 − *β*) of 0.8, and a margin error of 7%. Consulting relevant tables, we determine that the target sample size should be 251 individuals with an anticipated attrition rate of 10%, resulting in a final target sample size of 276 patients.

In addition, we conduct an analysis to determine the required sample size for the post-treatment follow-up experimental process in patients with FGIDs. Based on a literature review, the overall rate of improvement (P1) in FGIDs patients after receiving conventional treatment regimen is reported as 57% (37). We expect that patients with both FGIDs and psychological disorders will have an overall rate of improvement (P2) following conventional treatment at a ratio of 1: 2 compared to P1. The sample allocation between these two groups is set at 1: 1, with a test level *α* of 0.05, test efficacy (1 − *β*) of 0.8, and a loss rate of 10%. Through analysis using PASS software (V21.0.3), the target sample size is determined to be 98 individuals.

The specific distribution scheme of the sample can be observed in Figure 1.

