#### The evaluation metric for the diagnostic test

2.6.1

Primary Outcome: Sensitivity and specificity of vibraimage technology compared to HADS as the gold standard.

Secondary Outcomes: Positive predictive value (PPV), negative predictive value (NPV), and overall accuracy of vibraimage technology.

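### The 80% power stated for the diagnostic-accuracy sample size is not a property of that calculation: 251 is a confidence-interval-width result with no power in it

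*Protocol article*

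**What the plan says.** Section 2.6.1 of the protocol article names the primary diagnostic outcome as "Sensitivity and specificity of vibraimage technology compared to HADS as the gold standard". It gives no hypothesis, performance goal or minimum acceptable value.

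Section 2.7 sizes this part of the study from five inputs:
- Prevalence: "the prevalence of psychological disorders in FGIDs is 50" (per cent).
- Sensitivity: "we assume a sensitivity of 80% for vibraimage technology".
- Alpha: "a significance level (*α*) of 0.05", with sidedness not stated.
- Power: "a test power (1 − *β*) of 0.8".
- Precision: "a margin error of 7" (per cent).

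The section then reads: "Consulting relevant tables, we determine that the target sample size should be 251 individuals with an anticipated attrition rate of 10" (per cent), and arrives at 276. It names no formula and refers only to tables. Under section 2.2.3, data from patients who withdraw are left out of later analyses, so attrition reduces the number analysed.

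**The concern.** A margin of error and a power belong to two different kinds of calculation. A margin fixes the width of a confidence interval and needs no hypothesis. A power is the probability of rejecting a stated null value, and it cannot be defined without one. Section 2.7 gives both for a single number, and neither it nor section 2.6.1 supplies a null. If the number came from the margin alone, the power is a claim that the design does not support. A reader could then take 276 patients as giving an 80% chance of establishing the screening performance of the technology, when they give an estimate with an interval of a certain width.

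**Working it through.** **Inputs (section 2.7).** Sensitivity Se = 0.80; margin d = 0.07; prevalence π = 0.50; alpha = 0.05, taken as two-sided (z = 1.96); power 0.80 (z = 0.8416); attrition 10%.

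**1. Reproducing 251.** The precision formula for a proportion, scaled by prevalence, is

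N = z² × Se × (1 − Se) / (d² × π)

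- HADS-positive patients: 1.96² × 0.8 × 0.2 / 0.07² = 125.4
- Total: 125.4 / 0.50 = 250.9, so **251**. This is an exact match that uses every stated input except power.

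A one-sided alpha gives 177, so the two-sided reading is the one that fits.

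**2. Trying to bring power in.** None of these variants comes near 251:

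| Variant | Total N, two-sided | Total N, one-sided |
|---|---|---|
| (z for alpha + z for beta)² in place of z² | 513 | 404 |
| One-sample test, null 0.87, true 0.80 | 405 | 323 |
| One-sample test, null 0.80, true 0.87 | 465 | 361 |
| One-sample test, null 0.80, true 0.73 | 547 | 434 |
| One-sample test, null 0.73, true 0.80 | 594 | 465 |

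The one-sample rows use n = [(z_α √(p0(1 − p0)) + z_β √(p1(1 − p1))) / (p1 − p0)]², divided by 0.50. The null values are assumptions, because the article gives none.

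**3. Power that 251 patients would have.** With 125.5 HADS-positives and a true sensitivity of 0.80,

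power = Φ[(|0.80 − p0| − 1.96 √(p0(1 − p0)/125.5)) / √(0.16/125.5)]

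- p0 = 0.73: (0.07 − 1.96 × 0.0396) / 0.0357 = −0.215, power about **41%**
- p0 = 0.87: (0.07 − 1.96 × 0.0300) / 0.0357 = 0.313, power about **62%**

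With the null at 80% and the true value 7 points away, the power is about 50%. This is what sizing on the half-width alone produces: 1.96 standard errors then equal the 7-point difference.

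**4. Attrition.**
- 251 × 1.10 = 276.1, which is the stated 276.
- 276 × 0.90 = 248.4, so about 248 remain.
- Keeping 251 needs 251 / 0.90 = 278.9, so 279.
- Half-width: 1.96 √(0.16/125.5) = 7.00 points at 251, and 1.96 √(0.16/124) = 7.04 points at 248.

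**5. Precision with 248 evaluable patients.** Half-width = 1.96 √(0.16/m), where m is the number of HADS-positives (for sensitivity) or HADS-negatives (for specificity). The 80% specificity is an assumption; the article states none.

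| HADS-positive share | Positives | Sensitivity 80% | Negatives | Specificity 80% |
|---|---|---|---|---|
| 50% | 124 | ±7.0 | 124 | ±7.0 |
| 40% | 99.2 | ±7.9 | 148.8 | ±6.4 |
| 30% | 74.4 | ±9.1 | 173.6 | ±6.0 |

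**The case against.** The strongest reply is that the power is a stray parameter in an otherwise sound calculation. The 7-point margin stands in the same sentence, 276 delivers almost exactly that precision, and no analysis changes. This is right about the consequences, and it limits the point to a correction of wording. It does not make the stated power true.

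Two readings might rescue the 80%, and neither does:
- It could mean the chance that the observed interval is no wider than ±7 points. With 138 HADS-positives (all 276 completing) that chance is indeed about 80%. But 276 is derived as 251 plus attrition, and with 124 to 126 positives the chance is only about 46% to 54%.
- A null could be picked to fit. With about 125 positives, two-sided power is about 71% against 70% and about 86% against 68%. Choosing a null after the event is not the plan's hypothesis. For the same reason, a new statement of 80% power to exclude some lower sensitivity should not replace the old one.

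Some stronger inferences are tempting but unsupported:
- **That the true power is 41% and that 594 patients are needed.** This takes the least favourable of several assumed nulls. The article describes 7% as a margin of error and never proposes a test against 73%.
- **That section 2.7 inflates for attrition by two different rules.** The 98 for the follow-up comparison fits either. For 57% against 28.5%, an unpooled normal approximation gives 43.4, so 44 per group. Then 44 × 1.1 = 48.4 and 44 / 0.9 = 48.9 both round up to 49 per group.
- **That specificity is left unprotected.** At the stated 50% prevalence there are as many HADS-negatives as positives, so an 80% specificity has the same ±7.0. Its precision improves if fewer patients are HADS-positive.
- **That relying on 50% prevalence is an error.** It is a declared assumption that agrees with the Introduction. What is useful is to show how the precision changes with it.

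**Conclusion.** The power stated in section 2.7 for the diagnostic-accuracy sample size is wrong as written. The formula is inferred, since the article cites only tables, but the match is exact and no power-based variant tried gives a total between 177 and 323. The design offers a 95% interval of about ±7 points for a sensitivity of 80% when half the patients are HADS-positive. Read as power for a 7-point difference with a true sensitivity of 80%, 251 patients would give about 41% to 62% two-sided, depending on a null that has to be assumed.

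The attrition slip is real but minor: three patients, and 0.04 of a point in the half-width. The sample size itself remains adequate for the stated precision.

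**What to change.** In section 2.7, delete the power from the diagnostic-accuracy paragraph and describe the calculation as precision-based, naming the formula. State that 276 enrolled leaves about 248 evaluable at 10% loss, or correct the target to 279 if 251 evaluable patients are to be kept. Report the expected 95% half-widths at 50%, 40% and 30% HADS-positive: about 7.0, 7.9 and 9.1 points for 80% sensitivity, and 7.0, 6.4 and 6.0 points for an assumed 80% specificity. If a test of performance really is intended, the null value, the test and a matching sample size have to be stated instead.

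The precision wording costs a few sentences and the loss of a favourable-sounding figure. No patients are added if 276 is kept, and three are added if the target becomes 279.
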